### Randomization with double-blind and allocation concealment

The study has a prospective, randomized, double-blind, placebo-controlled, parallel-group design. Eligible patients are randomly assigned to one of the two treatment study groups, labelled the ‘melatonin group’ or the ‘placebo group’. Randomization is based on a computer-generated random digits table and follows a concealed process using sealed and numbered envelopes that allocate the patient to either of the two arms of the study. Patients may be randomized into this study only once, unless they were discharged from the hospital and were re-admitted more than 180 days after their first enrolment. The study does not allow crossover, and if any occur, they will be reported as protocol violations.

The experimental drug and a placebo with the same characteristics are prepared by a pharmacist. The patients and all study personnel except the investigative pharmacist are blinded to the treatment assignment. The details of the treatment assignments are unknown to any of the investigators and are contained in a set of opaque and sealed envelopes, each marked with only the randomization number.

### Trial interventions

All patients are randomized at a ratio of 1:1 to the oral melatonin or placebo group. Time zero (T0) is defined by randomization and the study treatment and relevant inspections are started just after. The baseline data about the sleeping state of the patients needs to be recorded on day 1 after enrolment, thus the intervention begins on day 2. The melatonin group patients receive 3 mg of melatonin orally or through a feeding tube at 9:00 pm for four consecutive nights (from day 2 to 5) once they have enrolled in the study. If melatonin is administered by a nasogastric (or nasojejunal) tube, the tablet should be crushed and mixed with 20 ml of water, followed by another 20 ml to flush out the remnants inside the tube. The placebo group patients will receive the placebo orally or through a tube using identical methods and at the same time as the patients in the melatonin group.

After randomization, given the possible powerful effect of the high level of noise, turning on of the lights, or the intensive routine care and procedures on patients’ sleep in the ICU, we will offer earplugs and eye masks to the patients and we will dim the main light at night (from 9:00 pm to 7:00 am). Meanwhile, meetings and posters were employed to encourage staff to minimise environmental, nursing and clinical disturbances, such as clustering patient care activities during the nocturnal study periods. Additionally, nurses should select time periods to promote sleep by avoiding routine ICU care activities (such as the daily bath), reducing ambient noise and turning down the lights during these periods. Other therapy and nursing projects should follow the clinical guidelines and nursing criterion.

In particular, during the sleep evaluation and intervention period (T0 time - 9:00 pm on day 6), pain, delirium and agitation will be managed in accordance with local guidelines. In case of clinical indication for analgesia and sedation, which can influence the effectiveness of melatonin and sleep structure, the study treatment is stopped and the necessary related administration is started according to the decision of the investigators. To help manage complex cases, three flowcharts are proposed for pain, sedation and delirium (Figures 
1,
2 and
3). They stress the importance of considering all of those factors (that is, organic and metabolic causes, noise and light, anxiety, the presence of invasive tools and pain) that could contribute to agitation, delirium and pain, and should be corrected before administering any neuroactive drug. Analgesics (particularly opiates) must be used only in case of pain (a Verbal Numeric Rating (VNR) score >3 or a Behavioral Pain Scale (BPS) score >6)
[44]. If delirium (CAM-ICU+) and agitation (RASS >0) appears, after correcting the underlying causes, the non-pharmacological protocol will be applied and potential deliriogenic therapies stopped; only after these interventions may physicians prescribe haloperidol or any other antipsychotic drug and remove these participants according to local guidelines. In these cases, the patient will stop taking the study drug but remain in the study and the investigator will perform the end-of-treatment assessments immediately and the end-of-study visit 28 days later. The trial procedures are shown in Figure 
4.

**Figure 1 Fig1:**
[figure not shown]
**A bedside flowchart for pain management in ICU patients.**
^1^Consider the patient not cooperative if: RASS < -2/CAM-ICU+/communication or linguistic barriers. ^2^Verbal Numeric Rating (VNR) 0 = no pain, 10 = maximal conceivable pain. Ask:“Can you quantify your pain between 0 and 10?”. Consider at rest and breakthrough pain (e.g. = coughing, tracheo-bronchial aspiration). ^3^Consider the evaluation as reliable if it takes into account the subjective parameters the patients uses to evaluate their pain: cultural, religious and familial aspects, expectation for secondary benefits. ^4^Behavioral Pain Scale (BPS) 0 = absence of pain, 12 = maximal pain. -Facial expression: 1. Relaxed/2. Partially tightened/3. Fully tightened/ 4. Grimacing. -Upper limbs: 1. No movement/2. Partially bent/3. Fully bent with finger flexion/4. Permanently retracted. -Compliance to ventilation: 1. Toleration movement/ 2. Coughing but tolerating ventilation for most of the time/ 3. Fighting ventilator/4. Unable to control ventilation.

**Figure 2 Fig2:**
[figure not shown]
**A bedside flowchart for agitation management in ICU patients.**
^1^Always aim for RASS target =0/-1 (patient awake and tranquil, well adapted despite invasive tool and critical condition). RASS target may be between -2 to -4 if required by clinical conditions. ^2^Sepsis, hypo-perfusion, hypo/hyperglycemia, hypoxia, fever, electrolyte imbalance, alkalosis/acidosis. ^3^Mode of ventilation; bladder catheter positioning; bronchial aspiration.

**Figure 3 Fig3:**
[figure not shown]
**A bedside flowchart for delirium management in ICU patients.**
^1^Sepsis, hypo-perfusion, hypo/hyperglycemia, hypoxia, fever, electrolyte imbalance, alkalosis/acidosis. ^2^None pharmacological protocol. Orientation: Use patient’s visual and auditory aids, Encourage communication calling the patient by name, Availability of patient’s personal belongings, Coherence between physicians and staff intervention, Use music or TV during the daytime. Environment: Lights off during the night, on during the daytime, Orient patients’ beds to allow vision of sunlight, Discourage sleep during the daytime, Patient mobilization and physiotherapy during the daytime, Control excessive noise during the daytime, Avoid medical and nursing procedures during the night. ^3^Consider to stop or decrease deliriogenic therapy: anticholinergic drug, metoclopramide, inhibitor of protonic pump, promethazine, etc.

**Figure 4 Fig4:**
[figure not shown]
**The trial procedures flow sheet.** ICU, Intensive care unit; PSG, Polysomnography; RCSQ, Richards Campbell sleep questionnaire; SOFA, Sequential organ failure assessment; VAS-A, Visual analogue scale-anxiety.

### End of participation in the study

Patients will leave the study when the following occurs: (a) the patient refuses to participate in the study; (b) an exclusion criterion appears during the course of the intervention; (c) a severe adverse event occurs; (d) the patient’s condition gets worse; (e) ICU discharge or death.

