**Table 1 Tab1:** **Definition of study objectives**

Objective	Definition
Objective sleep quality	Total sleep time, the length of sleep at night (9:00 pm - 7:00 am) and during the day (7:00 am - 9:00 pm), sleep architecture (NREM stage 1 and 2, SWS, REM), and sleep disruption (the number of arousals and duration of sleep), which will be monitored for one 24-hour period using a portable PSG device.
Subjective sleep quality	The subjective feelings of nightly sleep status of the patient, including sleep depth, wake time after sleep onset, number of awakenings after sleep onset, latency to sleep onset, and sleep quality. It will be evaluated using the RCSQ [38, 39].
Anxiety level	ICU anxiety is defined as a state marked by apprehension, agitation, increased motor activity, number of arousals, and fearful withdrawal during the ICU stay [40]. It will be assessed using the VAS-A.
Delirium-free days in 8 and 28 days	Number of days that the patient is not delirious over 8 and 28 days starting from the day of inclusion. Patients are diagnosed as delirious when they have at least one positive CAM-ICU screening during their ICU stay. A delirium-free day is defined as a negative CAM-ICU screening during that day. In case a delirious patient is discharged from the ICU, a delirium-free day is defined as a delirium observation scale score of less than 3 during a complete day [41].
Ventilator-free days in 28 days	Time in days that the patient is not on a mechanical ventilator. If the patient is ventilated mechanically, including invasive and non-invasive ventilation several times during one ICU admission, then the non-ventilator times are added. Ventilator-free days (in 28 days) will be calculated.
Antibiotic-free days in 8 and 28 days	Number of days that the patient does not require any antibiotics at 8 and 28 days from randomization will be calculated.
ICU length of stay	Duration of admission to the ICU.
Overall ICU mortality at 28 days	Survival time will be assessed. Patients will be classified as either alive at study day 28 or dead at study day 28. Differences between the two strategies in mortality rates will be evaluated using the assumption of asymptotic normality. Estimates of relative risks and odds ratios and the corresponding 95% confidence intervals will be presented.

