The sound and illuminance levels are recorded from day 1 to day 6 using the integrated sound pressure level meter and the illuminance level meter. Continuous equivalent sound pressure levels (Leq) in ‘A’ weighted decibels and peak sound pressure levels (Lpeak) in ‘C’ weighted decibels are logged every second. The illuminance level (in lux) is recorded once per minute using a sensor placed close to the patient’s head. The bedside nurse should be asked to log an event whenever the patient received treatment or care. The event log will contain the following items: clinical assessment, tracheal suctioning, pressure area care, physiotherapy, mouth or eye care, blood test (sampling), washing, non-invasive blood pressure, eating and drinking, dressing, pain, line insertion and X-ray. Drug records are compiled daily for drugs that are known to adversely affect sleep or melatonin pharmacokinetics.

At the time of the ICU discharge, patients’ data and vital statuses, lengths of mechanical ventilation, the number of days of antibiotics use, the number of delirium-free days, the length of the ICU stay and ICU mortality will be recorded.

To investigate the enteral absorption and metabolism of orally administered melatonin in critically ill patients during their ICU stay and to evaluate the serum melatonin levels and their circadian variations in these patients, the melatonin levels are measured in blood samples taken on days 1 and 2 (before the intervention) and days 5 and 6 (four days after the intervention) at 20:45 (before administration), 9:10 pm, 9:30 pm, 00:00 am, 3:00 am, 6:00 am, 2:00 pm and 8:00 pm in 20 patients from each group. The plasma levels of norepinephrine and cortisol are also measured at the same time points. In addition, plasma levels of SOD, MDA, catalase (CAT), IL-6 and IL-8 are measured at 07:00 am on days 2 and 6.

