### Statistical analysis

All analyses will be performed according to the intention-to-treat principle, that is, all randomized patients will be analysed in the groups to which they were originally allocated and will be blinded to treatment assignment. Baseline patient characteristics will be compared and described using the appropriate statistics. Categorical variables will be presented as the numbers and percentages and will be analyzed by the *χ*^2^- tests or Fisher’s exact tests, or when appropriate, as relative risks. Continuous variables will be checked for normal distribution by the Kolmogorov-Smirnov test. Normally distributed variables will be expressed by their mean and standard deviation; non-normally distributed variables will be expressed by their medians and 95% confidence levels. Comparisons of continuous variables will be performed using Student’s *t*-test for normally distributed variables and the Mann-Whitney U test for non-normally distributed variables. Appropriate (linear, logistic, or Poisson) regression will be generated for the identification of the determinants of outcomes and for the correction of baseline covariates.

One-way repeated measures analysis of variance (ANOVA) were used to determine differences in the sleep variables, the subjective sleep quality, anxiety levels and plasma levels of melatonin, cortisol and norepinephrine. Twenty-eight day mortality will be analysed according to the Kaplan-Meier method and the results will be compared with the log-rank test hazard ratios and reported with 95% confidence limits. The number of delirium-free days, ventilation-free days and antibiotics-free days will be tested by Student’s *t*-test for normally distributed data and the Mann-Whitney U-test for non-normally distributed data. The differences in adverse events between the intervention and placebo groups are used for safety analyses. All tests of significance will be at the 5% significance level and two-sided. All of the data in this trial will be assessed with SPSS Statistics version 20.0 (SPSS, Chicago, Illinois, United States). The main analysis will be fully specified before unmasking.

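### Ending participation at ICU discharge contradicts the 28-day mortality and free-day outcomes, which need data on every patient to day 28

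*Protocol article*

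**What the plan says.** **Exit from the study.** In the protocol article, End of participation in the study, the last listed reason for leaving is "e) ICU discharge or death". Two other reasons are "c) a severe adverse event occurs; (d) the patient’s condition gets worse". The sentence concerns leaving the study, not stopping the study drug.

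**When outcomes are recorded.** Data collection and management places the recording "At the time of the ICU discharge". Besides vital status and length of ventilation, it lists "the number of days of antibiotics use, the number of delirium-free days, the length of the ICU stay and ICU mortality will be recorded". It describes no later collection.

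**What the outcomes need.** For mortality, Table 1 states: "Patients will be classified as either alive at study day 28 or dead at study day 28". It sets a 28-day horizon for ventilator-, antibiotic- and delirium-free days. For delirium it also looks past the ICU: "In case a delirious patient is discharged from the ICU, a delirium-free day is defined as a delirium observation scale score".

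**What is analysed.** Statistical analysis promises intention to treat for all randomized patients and states: "Twenty-eight day mortality will be analysed according to the Kaplan-Meier method". It adds a log-rank test and hazard ratios. Table 1 plans relative risks and odds ratios for the same outcome, which it labels ICU mortality.

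**A later visit for some.** Trial interventions keeps certain patients who stop the study drug in the study, with an end-of-study visit 28 days after their end-of-treatment assessments.

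**The concern.** A patient discharged alive from the ICU before day 28 has, under the exit rule, left the study. Table 1 still needs that patient's status on day 28 and a count of ventilator-, antibiotic- and delirium-free days up to then. An analysis plan cannot recover data that the protocol stops collecting.

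Discharge before day 28 is foreseeable, because eligible patients must be stable and ready to be weaned. The gap is not neutral either: patients leave the ICU alive because they are better, and ICU length of stay is itself a secondary outcome. If melatonin changed ICU stay, it would also change how long each arm is observed for the other 28-day outcomes.

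The mortality endpoint adds a second ambiguity. Its name refers to death in the ICU and its definition to status at day 28. These are different quantities once patients leave the ICU alive.

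**Working it through.** The document gives no death rate, discharge rate or censoring rule, so there is no stated figure to reproduce. The check sets the passages against each other, then shows what follows under assumed rates.

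**1. One patient, discharged alive on day 10**

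| Outcome | Needed (Table 1) | Available if the exit rule is followed |
|---|---|---|
| Mortality | status at day 28 | status at day 10 |
| Ventilator-free days | to day 28 | use to day 10 |
| Antibiotic-free days | to days 8 and 28 | use to day 10; the 8-day count is complete |
| Delirium-free days | to days 8 and 28, with a score after ICU discharge if delirious | screening to day 10; no collection after discharge described |

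The unobserved stretch is 28 − 10 = 18 days. With u days of use up to discharge, stopping the count at discharge gives 10 − u free days. Subtracting recorded use from 28 gives 28 − u. The two conventions differ by 18 days for any u, and neither is verified by data.

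**2. Whether the visit in Trial interventions fills the gap**

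It covers only patients who stop the study drug, and it is timed from end of treatment. A patient who stops on day 3 would be seen on day 3 + 28 = 31. It gives nothing for a patient who completes treatment and goes to the ward.

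**3. If Kaplan-Meier were censored at discharge: ICU death**

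Assumptions: constant hazards; by day 28, 15% have died in the ICU, 70% have been discharged alive and 15% are still there.

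- Total hazard h: exp(−28h) = 0.15, so h = 0.0678 per day.
- Death hazard: h × 0.15/0.85 = 0.0120 per day.
- Kaplan-Meier estimate at day 28: 1 − exp(−28 × 0.0120) = 0.285, or 28% with the unrounded hazard.
- Cumulative incidence of ICU death: 15%, by assumption.

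For a range, let hd be the ICU death hazard and hr the discharge hazard. Kaplan-Meier gives 1 − exp(−28hd). The cumulative incidence is hd/(hd + hr) × [1 − exp(−28(hd + hr))]. With hd from 0.005 to 0.02 per day and 1/hr from 7 to 21 days (both assumed), Kaplan-Meier runs from 13.1% to 42.9% and the cumulative incidence from 3.3% to 25.1%. Kaplan-Meier is higher in every case, by a factor of about 1.7 to 4.

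**4. The same curve read as all-cause 28-day mortality**

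With hp the death hazard after discharge, all-cause mortality is

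1 − exp(−28(hd + hr)) − hr × [exp(−28hp) − exp(−28(hd + hr))]/(hd + hr − hp).

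For hd = 0.01 and 1/hr = 14 days, Kaplan-Meier censored at discharge gives 24.4%:

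| hp/hd | All-cause mortality at day 28 | Kaplan-Meier is |
|---|---|---|
| 0 | 11.0% | too high |
| 0.25 | 14.6% | too high |
| 0.5 | 18.1% | too high |
| 1 | 24.4% | correct |
| 1.5 | 30.1% | too low |

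Exits (c) and (d) remove patients who are deteriorating. Censoring them would push the estimate down, and the document does not say how many there may be.

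**The case against.** The strongest reply is that later follow-up was plainly intended. Table 1 asks for day-28 status and scores delirium after discharge, and Trial interventions has a later visit. The procedures flow sheet (Figure 4) is not available here and may bear on this. That stands as far as it goes: the defect is a contradiction. A reader might infer that the 28-day outcomes are definitely cut off at discharge, but the document does not settle this. The post-discharge delirium rule, however, covers only patients who were delirious, and the later visit only those who stopped the drug. Neither supplies vital status, ventilation or antibiotic data for other discharged patients.

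Four further readings go beyond the text:

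- **Kaplan-Meier is censored at discharge.** No section says so, and a censoring rule is normally left to the analysis plan. Patients with a day-28 status would be followed to day 28. If ICU death is meant, keeping patients discharged alive event-free to day 28 reproduces the cumulative incidence.
- **Mortality is overstated.** This holds for ICU death under that censoring. For all-cause mortality it needs a lower death hazard after discharge, which is plausible but not given.
- **Earlier discharge lowers the free-day score.** Days of ventilation and antibiotic use are recorded, so they could be subtracted from 28, and early discharge could then score better.
- **Two mortality analyses are an error.** A relative risk at day 28 and a survival curve are common companions.

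The illustration also concerns the level of one curve. A log-rank test with discharge censored would still compare ICU death hazards between arms, and no between-arm bias has been computed.

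**Conclusion.** The point holds as an internal contradiction that leaves the 28-day secondary outcomes without a sound data source. Followed as written, the exit rule and discharge-time recording deny day-28 status to every patient discharged alive earlier, and leave the rest of each free-day count unverified (18 of 28 days for a discharge on day 10). Observation time then depends on an outcome that treatment may affect.

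The 28% against 15% figure shows what censoring at discharge would do to ICU mortality. It rests on assumed constant hazards and an assumed split of deaths and discharges. Neither the direction for all-cause 28-day mortality nor the size of any treatment-comparison bias can be derived from the document. The point concerns these secondary outcomes and makes no claim about the polysomnography outcome.

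**What to change.** Reconcile Table 1, Trial interventions, End of participation in the study, Data collection and management, and Statistical analysis:

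1. Separate the end of study treatment from the end of follow-up. ICU discharge, and the other events that end treatment, should not end outcome collection. When the study drug is stopped is a separate matter that this change does not touch.
2. For all randomized patients who have not withdrawn consent, collect vital status, ventilation, antibiotic and delirium data to day 28 from randomization, regardless of ICU discharge, from ward records or by telephone.
3. Give mortality one definition. Either use all-cause death by day 28, with administrative censoring at day 28, or, if ICU death is meant, treat discharge alive as a competing event. The relative risk and the Kaplan-Meier analysis may both stay if they share that definition.

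The cost is amendment wording and a small amount of follow-up work for each discharged patient. The existing later visit does not already supply these data, so the work is additional. For patients already past day 28, ward records may be the only source.

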### Data collection and management

Trained staff will record data and fill in the web-based collection forms. At the moment of patient inclusion, patient data on demographic characteristics and the history of past illnesses will be collected: age, sex, height and weight, Acute Physiology and Chronic Health Evaluation II(APACHE II) score, Sequential organ failure assessment(SOFA) score, Glasgow coma scale(GCS) score, diagnosis, and comorbidities. Clinical, physiological and analytical variables such as vital signs (temperature (T), blood pressure (BP), heart rate (HR), and respiratory rate (RR)), routine ICU laboratory tests (white blood count (WBC), serum creatinine (SCr), blood urea nitrogen (BUN), alanine aminotransferase (ALT), and aspartate aminotransferase (AST)) will be recorded at the moment of inclusion. The duration of time of ventilation, ventilation mode, the number of days in delirium, the ICU length of stay and the names, dose, duration of use and time of last use of sedatives, analgesics medications and vasopressor drugs will also be recorded prior to study inclusion.

Furthermore, sleep-related baseline data, including objective and subjective sleep quality and anxiety levels should be recorded. Subjective sleep quality, including the TST, the length of sleep at night (9:00 pm to 7:00 am) and in the day (7:00 to 9:00 pm), sleep architecture (NREM stage 1 and 2, SWS and REM), sleep disruption (the number of arousals and the duration of sleep), will be monitored for one 24-hour period using a portable PSG device from day 1 9:00 pm to day 2 9:00 pm. The PSG remains the gold standard for sleep quality assessment. Electroencephalographs (EEG; O1/M2, C4/M1), electromyographs (EMG), electrooculographs (EOG; right and left) and electrocardiographs (ECG; lead II) will be recorded. The patients’ skin will be prepared according to standard techniques. Gold cup EEG electrodes will be placed at O1/M2 and C4/M1 according to the International 10 to 20 System. Two EOG electrodes will be used for the right and left eye movements. The EMG electrodes will be located over the right and left masseter (facial) muscles. The electrode application will be performed by the specialist.

The subjective sleep quality refers to the subjective feelings of the nightly sleep status of the patients. The baseline nightly sleep perceptive quality (day 1 9:00 pm to day 2 7:00 am) will be evaluated using the RCSQ at 9:00 am on day 2. The RCSQ contains five 100 mm visual analogue scales (VAS): sleep depth, latency, awakenings, time awake and quality of sleep (higher scores indicate better sleep). The RCSQ was pilot tested in a medical ICU and validated with overnight PSG in medical ICU patients. In our study, patients who are unable to write were assisted; the patients used their current communication strategy to indicate where the investigator should mark the VAS.

Anxiety is defined as a state marked by apprehension, agitation, increased motor activity, arousal, and fearful withdrawal. The baseline anxiety levels are assessed on day 2 at 9:00 am via self-report using the 100 mm VAS-A, which is presented to patients with a vertical orientation such as a thermometer. The bottom of the scale is the statement ‘not anxious at all’ and the top is “most anxious ever.” Patients indicate their current level of anxiety in response to ‘How are you feeling today?’. The VAS-A score is the number of millimetres from the bottom edge of the line (not anxious at all) to the patient’s mark. The VAS-A and the Spielberger State Anxiety Inventory are correlated (r = 0.4916 to r = 0.8219), demonstrating concurrent validity.

During the intervention period (days 2 to 5), outcome-related data, such as the objective and subjective sleep quality, and the anxiety level should be recorded. Analyses are limited to the fourth day (day 5 at 9:00 pm to day 6 at 9:00 am) because the potential chronophypnotic benefits of melatonin are not immediate and may take at least three days to be realised. Therefore, objective sleep quality should be monitored for one 24-hour period using the PSG from day 5 at 9:00 pm to day 6 at 9:00 pm, and the associated parameters and methods as described in the ‘Methods/Design’ section. Meanwhile, the subjective sleep quality and anxiety levels should be evaluated at 9:00 am on day 6 and the related methods have been previously described. In addition, daily information including the vital signs and lab parameters, the SOFA score, neurological monitoring (RASS, CAM-ICU, and GCS), as well as the mode, parameter and duration of mechanical ventilation should be recorded.

The sound and illuminance levels are recorded from day 1 to day 6 using the integrated sound pressure level meter and the illuminance level meter. Continuous equivalent sound pressure levels (Leq) in ‘A’ weighted decibels and peak sound pressure levels (Lpeak) in ‘C’ weighted decibels are logged every second. The illuminance level (in lux) is recorded once per minute using a sensor placed close to the patient’s head. The bedside nurse should be asked to log an event whenever the patient received treatment or care. The event log will contain the following items: clinical assessment, tracheal suctioning, pressure area care, physiotherapy, mouth or eye care, blood test (sampling), washing, non-invasive blood pressure, eating and drinking, dressing, pain, line insertion and X-ray. Drug records are compiled daily for drugs that are known to adversely affect sleep or melatonin pharmacokinetics.

At the time of the ICU discharge, patients’ data and vital statuses, lengths of mechanical ventilation, the number of days of antibiotics use, the number of delirium-free days, the length of the ICU stay and ICU mortality will be recorded.

To investigate the enteral absorption and metabolism of orally administered melatonin in critically ill patients during their ICU stay and to evaluate the serum melatonin levels and their circadian variations in these patients, the melatonin levels are measured in blood samples taken on days 1 and 2 (before the intervention) and days 5 and 6 (four days after the intervention) at 20:45 (before administration), 9:10 pm, 9:30 pm, 00:00 am, 3:00 am, 6:00 am, 2:00 pm and 8:00 pm in 20 patients from each group. The plasma levels of norepinephrine and cortisol are also measured at the same time points. In addition, plasma levels of SOD, MDA, catalase (CAT), IL-6 and IL-8 are measured at 07:00 am on days 2 and 6.

